# Lay health coaching intervention for older adults with chronic diseases: study protocol for a pragmatic randomised controlled trial

**DOI:** 10.1186/s13063-024-08649-x

**Published:** 2024-12-18

**Keywords:** Chronic disease, Self-management, Patient activation, Health coaches, Pragmatic, Randomised control trial

## Abstract

**Background:**

A large proportion of older adults suffer from chronic diseases. Health coaching is a promising intervention that enhances individuals’ health knowledge and supports changes in health behaviours. Even though health professionals usually conduct health coaching interventions, lay health workers from different backgrounds account for a growing segment of health coaches over the years. The planned study’s main objective is to investigate whether health coaching by lay health workers is as effective as that by health professionals.

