### Objectives {7}

This study aims to (1) examine the effects of health coaching in community-dwelling older adults with various chronic diseases, and (2) compare the effects of two types of health coaches (i.e. health professionals and lay health workers) on health coaching outcomes. The effectiveness of health coaching is often measured through individual changes in health knowledge and behaviours, psychological status and clinical outcomes [36, 44]. With reference to previous health coaching studies [40, 43, 45, 46], the present study will measure patient activation, physical activity and nutrition behaviours as primary outcomes and depressive symptoms, body mass index (BMI) and systolic and diastolic blood pressure as secondary outcomes. This study hypothesised that the primary and secondary outcomes will be improved after participation in health coaching, and the improvements in health coaching delivered by lay health workers are comparable to those delivered by health professionals.

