#### Sample size {14}

The required sample size is estimated for one of the primary outcomes, i.e. patient activation. With reference to previous studies of patient activation interventions on chronic disease self-management [43, 61], the sample size is estimated on the basis of an effect size *f* = 0.2. Using G*Power, power analyses revealed that a total sample size of 266 is required to detect differences amongst the two intervention conditions (i.e. health coaching delivered by lay health workers vs. health professionals), using a multivariate analysis of variance with an effect size of 0.2, a power of 90% and an alpha level of 0.05, with 133 individuals in each condition. Considering the dropout rate of 30% over a period of three months, the target sample size is adjusted to 380 (with 190 individuals in each condition).

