## Statistical methods

### Statistical methods for primary and secondary outcomes {20a}

Descriptive statistics will be used to summarise participants’ baseline demographics and outcome variables throughout the study time points. Attrition analysis and randomisation tests will be carried out to test for differences in demographic and outcome variables between the intervention and comparison groups. Repeated measures ANCOVA will be conducted to examine any significant improvements in the primary and secondary outcomes across baseline and 3-month follow-up assessments whilst controlling for the effects of demographics (i.e. age, sex, education, chronic diseases) and the frequency of intervention sessions. Generalised estimating equation (GEE) analyses will be conducted to compare the primary and secondary outcomes at the 3-month follow-up between the intervention and comparison groups whilst controlling for the effects of demographics and the frequency of intervention sessions. The intention-to-treat principle will be adopted in the analyses for all the primary and secondary outcomes by imputing missing follow-up outcome data with their baseline values (i.e. assuming no change after the intervention for the primary and secondary outcomes) under the assumption of data being missing not at random. This assumption is plausible in the sense that missing data because of dropouts or non-responses are more likely amongst old-old participants with severe health problems. All statistical analyses will be conducted using R software. The treatment effect within and between the two groups will be assessed using Cohen’s *d* statistic [64].

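### The stated aim is that lay coaching is as effective as professional coaching, but the trial is sized and analysed to detect a difference and gives no margin or other criterion for comparability

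*Protocol article*

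**What the plan says.** The Abstract (Background) gives the study's "main objective is to investigate whether health coaching by lay health workers is as effective as that by health professionals". Objectives {7} turns this into a hypothesis that "the improvements in health coaching delivered by lay health workers are comparable to those delivered by health professionals", and the main Discussion asks the same question again.

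Sample size {14} is built on patient activation. It states that "the sample size is estimated on the basis of an effect size *f* = 0.2", chosen "With reference to previous studies of patient activation interventions on chronic disease self-management", and that "a total sample size of 266 is required to detect differences amongst the two intervention conditions". The calculation is described as "using a multivariate analysis of variance with an effect size of 0.2, a power of 90% and an alpha level of 0.05". That makes 133 per arm. Allowing for 30% dropout, the target becomes 380, or 190 per arm.

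Statistical methods {20a} uses GEE "to compare the primary and secondary outcomes at the 3-month follow-up between the intervention and comparison groups", with Cohen's d for effects within and between groups. The primary analysis is by intention to treat, and a missing follow-up value is replaced by the participant's baseline value. Section {20b} adds a complete-case analysis, and multiple imputation if data missing completely at random is not supported.

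The article contains no non-inferiority or equivalence margin, no one-sided or two one-sided test, and no confidence-interval rule for calling the arms comparable.

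**The concern.** The between-arm hypothesis is one of similarity, while the design tests for difference. Such a test can refute the hypothesis but cannot support it: failing to reject shows only that the data were not precise enough to separate the arms. The 90% power figure does not describe the chance of establishing what the trial sets out to establish.

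The article intends to act on the answer. Its abstract says that, if effectiveness is shown, lay workers should be included in delivering such programmes to lessen over-reliance on professionals. Its Discussion foresees evidence for integrating them into the healthcare system. Those conclusions need a bound on how much worse lay coaching could be, and the plan sets none.

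**Working it through.** **Inputs.** From {14}: f = 0.2, alpha 0.05, power 90%, 133 evaluable per arm, 30% dropout, 190 randomised per arm. From {20a}: baseline values replace missing follow-up values. Margins, the baseline correlation r and equal dropout in both arms are assumptions. Differences are in SD units.

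**1. The plan's own figure.** With two groups, d = 2f = 0.4. A two-sided two-sample t test (the same as a one-way F test) at alpha 0.05 needs 133 per arm, 266 in total, with power 90.1%. Then 266 / (1 − 0.30) = 380. Both figures reproduce exactly as a single-outcome test of difference.

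**2. Precision with 133 completers per arm.** SE = √(2/133) = 0.1226 SD, so the 95% CI half-width is 1.96 × 0.1226 = 0.24 SD.

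**3. Chance of a non-significant result when lay coaching is truly worse by d.** This is approximately Φ(1.96 − d/SE).
- d = 0.2: Φ(1.96 − 1.631) = 63%
- d = 0.3: Φ(1.96 − 2.447) = 31%
- d = 0.4: Φ(1.96 − 3.262) = 10%

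**4. The planned primary analysis.** Here 190 per arm are analysed, so SE = √(2/190) = 0.1026. Assume that 30% in each arm have baseline carried forward and that the SD is unchanged. A true difference d then appears as 0.7d.
- d = 0.2 becomes 0.14: Φ(1.96 − 1.365) = 72%
- d = 0.3 becomes 0.21: Φ(1.96 − 2.047) = 47%

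The larger analysed set does not make up for the shrinkage, so the imputation favours similarity.

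**5. Non-inferiority power with 133 per arm** (one-sided 2.5%, true difference 0): Φ(M/SE − 1.96).

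| Margin M (SD) | Power | Evaluable / randomised for 90% |
|---|---|---|
| 0.4 | 90% | 264 / 378 |
| 0.3 | 69% | 468 / 669 |
| 0.2 | 37% | 1052 / 1503 |

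**6. Effect of baseline adjustment.** SE is multiplied by √(1 − r²). At M = 0.3, power is 73% for r = 0.3, 81% for r = 0.5 and 93% for r = 0.7. The article gives no r.

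**7. A margin alone is not enough.** Take M = 0.3 and a true deficit of exactly 0.3, under the assumptions of step 4. The test would declare non-inferiority with probability Φ((0.3 − 0.21)/0.1026 − 1.96) = Φ(−1.08) = 14%, against a nominal 2.5%. A margin therefore has to be paired with an analysis that does not carry baseline forward.

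**The case against.** **No rule equates non-significance with comparability.** A reader might infer that the team will read p > 0.05 as comparable. The article never says so, and it plans to report Cohen's d between groups. This stands. What the document supports is narrower: it offers no criterion at all for its own hypothesis.

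**The analysis plan may supply the rule.** An interval rule could sit in a document that is not shown. That would not cure the mismatch, because the article itself fixes the hypothesis, the effect size and a sample size for a test of difference.

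**The sample may be large enough.** At a margin of 0.4 SD, non-inferiority needs 264 evaluable, almost the planned 266. This stands, so the point is not that the trial is too small. But 0.4 SD is the sizing effect, and nothing presents it as a tolerable loss between two active arms.

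**Is 0.4 SD the whole benefit of coaching?** That is tempting but unsupported. Section {14} says only that f was chosen by reference to two earlier studies. The Introduction describes one of them, a trial within a cohort, as finding no significant improvement in patient activation against usual care.

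**The stakes should not be inflated.** The article speaks of reducing over-reliance and of a collaborative model, not of replacing professionals.

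**Conclusion.** The point holds as a mismatch within the protocol article: the aim is similarity, while the sizing and the test are for difference, with nothing to connect them. The stated 90% is not power for the main objective. A non-significant GEE result would be weak evidence: it would occur 63% of the time with a true 0.2 SD deficit and 31% with 0.3 SD among 133 completers per arm. In the primary analysis the figures are about 72% and 47%.

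The completer figures rest on the article's own n and a normal approximation. The primary-analysis figures also assume 30% dropout in each arm and an unchanged SD. The non-inferiority powers assume margins that the article does not give. Objective 1, improvement after coaching, is a separate question and does not settle the comparison between arms.

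**What to change.** Before any unblinded comparison:

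1. Restate the between-arm hypothesis as non-inferiority of lay to professional coaching on patient activation at 3 months, with one justified and dated margin.
2. Conclude *as effective as* only if the lower limit of the two-sided 95% CI for lay minus professional lies above minus the margin. Require the conclusion to hold in the complete-case or multiple-imputation analyses that {20b} already plans.
3. Restate the power at 380 randomised for that margin.
4. If no margin can be justified at this stage, report the estimate with its 95% CI, state that a non-significant p-value is not evidence of comparability, and drop *as effective as* and *comparable* from the conclusions.

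Timing matters. Trial status expects recruitment to end in December 2024, the month of publication, and follow-up in March 2025. A margin set now comes late, and item 4 may be the more realistic course.

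The cost is protocol and analysis-plan wording plus a registry update; no extra participants are asked for. The stated power falls, materially so for margins below 0.4 SD.

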**Methods:**

The effects of health coaching intervention by lay health workers will be examined in comparison with that by health professionals within a single-blind, multi-centre, randomised controlled trial with a follow-up assessment after 3 months. A total of 380 community-dwelling older adults with chronic diseases will be recruited and randomly assigned using a 1:1 ratio into the intervention and control groups. The intervention group will receive a 3-month health coaching intervention delivered by lay health workers, whereas the control group will receive the intervention delivered by health professionals. Primary outcomes include patient activation, physical activity and nutrition behaviours.

**Discussion:**

The expected findings of this study will advance the health coaching literature, research and practice by determining whether health coaching by lay health workers is as effective as that by health professionals in enhancing older adults’ knowledge, skills and confidence in chronic disease self-management and promoting changes in health behaviours. If proven effective, the inclusion of lay health workers in delivering effective self-management interventions should be advocated to reduce the over-reliance on health professionals in the primary healthcare system.

**Trial registration:**

ISRCTN, ISRCTN73836238. Registered 8 November 2023.

**Supplementary Information:**

The online version contains supplementary material available at 10.1186/s13063-024-08649-x.

## Administrative information

Note: The numbers in curly brackets in this protocol refer to SPIRT checklist item numbers. The order of the items has been modified to group similar items (see https://www.equator-network.org/reporting-guidelines/spirit-2013-statement-defining-standard-protocol-items-for-clinical-trials/).

## Introduction

### Background and rationale {6a}

Due to decreased birth and mortality rates, the global population aged 60 years and above is projected to increase from 10% in 2022 to 16% in 2030 [1, 2]. With the upward shift in age distribution, the prevalence of chronic diseases is increasing. More than half of the adult population worldwide aged 60 years and above suffers from two or more chronic diseases, such as hypertension, diabetes and heart disease [3]. Previous studies show that individuals with chronic diseases are often associated with increased depression and decreased quality of life, particularly amongst those with poor control of health risk factors and comorbidities [4, 5]. Furthermore, chronic diseases place a substantial financial strain on the healthcare system. For instance, the total cost in the United States for the direct treatment of chronic diseases was more than $1 trillion in 2016 [6]. A systematic review of the financial burden related to chronic diseases indicated that chronic diseases accounted for at least 25% of healthcare budget in the European Union between 2008 and 2018 [7]. Therefore, with the increasing number of older adults with chronic diseases and the associated costs to the healthcare system, effective self-management of chronic diseases amongst older adults becomes increasingly important to alleviate financial strain on the healthcare system and ensure the quality of their prolonged lifespan [8].

In the past two decades, health coaching has emerged as an often-espoused and promising intervention to support individuals living with chronic diseases in setting self-care goals and initiating behavioural changes to improve health outcomes and quality of life [9–11]. Broadly defined, health coaching is patient-centred, focusing on patient-determined goals, incorporating self-discovery and active learning, encouraging accountability for behavioural goals and providing some health education alongside the coaching. It is facilitated by someone who is trained in behavioural change, communication and motivational interviewing skills [12]. Through a collaborative partnership with health coaches, health coaching aims to enhance patients’ medical and self-care knowledge, self-efficacy in chronic disease management and engagement in a healthy lifestyle [13, 14]. Although evidence shows the effectiveness of health coaching in increasing self-efficacy [15, 16] and improving health behaviours, such as physical activity, weight control and medication adherence [17–20], how different intervention components, such as the professional experience of health coaches and modalities of health coaching (e.g. face-to-face, telephone or electronic), are necessary for its effectiveness remains to be understood. Such a study could provide evidence of the efficacy of health coaching across different types of coaching [21] and help standardise health coaching interventions and optimise their effectiveness [11, 22]. For example, a systematic review evaluating the modalities of pharmacist health coaching found that favourable clinical outcomes were reported in each of the 12 reviewed studies regardless of the health coaching modality [23]. This finding suggested that no superior modality of pharmacist health coaching. To further explore the effects of intervention components, the present study therefore aims to examine how different types of health coaches may influence the effectiveness of health coaching.

In health coaching, health coaches take on the role of improving patients’ health literacy and guiding them to set and achieve realistic health goals through educational materials, patient-centred communication and empowerment [24, 25]. On the basis of their clinical experience, health coaches can be broadly categorised into two groups: health professionals and lay health workers [22]. Health professionals encompass various clinical practitioners, such as physicians, nurses, dieticians, pharmacists and students in these fields. By contrast, lay health workers usually do not possess specified credentials or regulated professional status. Examples include certified health coaches, health promotion workers and graduates of health-related fields (e.g. public health, nutrition and physiology). With profound clinical experience in treating chronic diseases and knowledge of medication management, health professionals are primarily considered to fit the role of health coaches [26, 27]. However, lay health workers from various backgrounds account for a growing segment of health coaches over the years [10, 28, 29]. In many low- and middle-income countries, lay health workers are increasingly recognised for their role in improving health equity for marginalised groups [30]. They tend to share similar values, socioeconomic status and/or cultural backgrounds with patients [31], and their interactions with patients are seen as non-hierarchical and less stigmatising than those with health professionals [32, 33]. Thus, patients are more inclined to engage with a health coach who is a lay health worker, particularly when the health coaching intervention is community-based.

Although lay health workers are increasingly taking up the role of health coaches [12], early systematic reviews of health coaching often purposefully exclude interventions delivered by lay health workers and focus mainly on studies published in English [20, 34]. Therefore, some researchers have advocated for paying more attention to the effectiveness of lay health coaching [21]. Few studies of lay health coaching have shown positive effects on self-management of chronic conditions (e.g. glycaemic and blood pressure control) and behavioural changes (e.g. physical activity and nutrition behaviours) [10, 35, 36]. For example, Willard-Grace et al. [10] found that a 9-month lay health coaching has improved inhaler adherence and technique amongst middle-aged and older American patients with moderate to severe chronic obstructive pulmonary disease (COPD). However, similar to health coaching delivered by health professionals [34], previous systematic reviews of lay health coaching for diabetes found that lay health workers varied in their ways of supporting, educating, advocating for and facilitating patients’ self-management [37, 38], resulting in disparate findings. For example, Dye et al. [39] did not find significant differences in emergency care use and hospital admission rates between lay health coaching and control groups in a small sample of older patients with cardiovascular diseases, congestive heart failure and diabetes. Therefore, whether health coaching delivered by lay health workers is as effective as that delivered by health professionals requires further examination, especially when the design of health coaching intervention (e.g. target population, intervention duration, and method of delivery) varies across studies.

This study will pay particular attention to the effects of lay health coaching on community-dwelling older adults with diverse chronic diseases. Previous health coaching studies were often conducted on relatively younger patients, with at least half of the participants being under 60 years [16, 40–42]. Whether health coaching is still effective in older adults, particularly those with low educational attainment, remains uncertain. Furthermore, health coaching studies have often focused on specific diseases such as diabetes and COPD [16, 41]. Consequently, the findings of these studies may not be generalisable to older adults with multimorbidity, which constitutes over 50% of the older population worldwide [3]. For example, by using trials within cohort design, Panagioti et al. [43] found that although older adults with multimorbidity participating in a 6-month telephone health coaching demonstrated lower levels of emergency care use, their patient activation, quality of life and risk of depression did not significantly improve compared with those with only usual care. To address these knowledge gaps, the present study adopts a randomised controlled trial (RCT) design to compare the effects of health coaching interventions delivered by lay health workers and health professionals in community-dwelling older adults with diverse chronic diseases.

### Objectives {7}

This study aims to (1) examine the effects of health coaching in community-dwelling older adults with various chronic diseases, and (2) compare the effects of two types of health coaches (i.e. health professionals and lay health workers) on health coaching outcomes. The effectiveness of health coaching is often measured through individual changes in health knowledge and behaviours, psychological status and clinical outcomes [36, 44]. With reference to previous health coaching studies [40, 43, 45, 46], the present study will measure patient activation, physical activity and nutrition behaviours as primary outcomes and depressive symptoms, body mass index (BMI) and systolic and diastolic blood pressure as secondary outcomes. This study hypothesised that the primary and secondary outcomes will be improved after participation in health coaching, and the improvements in health coaching delivered by lay health workers are comparable to those delivered by health professionals.

### Trial design {8}

This study is a single-blind, multi-centre RCT with a two-group pre-test and post-test between-groups design, in accordance with SPIRIT guidelines [47]. It delivers a 3-month health coaching intervention either by lay health workers (intervention group) or health professionals (comparison group) to community-dwelling older adults with chronic diseases. Survey measurements of primary and secondary outcomes will be taken before and immediately after the intervention. The study will compare the effects of the intervention and control groups at 3 months.

